#### Women’s experiences

Two questionnaires have been developed for administration at 36 weeks gestation (during pregnancy) and at 6–8 weeks post-partum (after the birth). These will enable women to report on their experiences with the model of care, their planned mode of birth (VBAC or CS) and the factors influencing the mode of birth choice. Distress and anxiety will be assessed using the Depression Anxiety Stress Scale (DASS 21) [33] and Edinburgh Postnatal Depression Scale (EDPS) [34]. Decisional conflict, knowledge, and anxiety will be assessed using measures from a previous Australian study [24].

The postnatal questionnaire includes questions about their labour and birth experiences and satisfaction with their decisions. With permission, we have adapted questions about the experience of care from surveys used to assess satisfaction in the COSMOS Study which examined the impact of caseload midwifery care on low risk women in Melbourne, Australia [29].

Both questionnaires were piloted with pregnant and postpartum women. Completion of each took approximately 20 minutes and they were reported to be understandable to the average adult reader.

#### Administration of questionnaires

The questionnaires have been professionally designed and printed. The women will be posted the questionnaires with a self-addressed envelope with a reply-paid stamp. The RA will contact participants to inform them that the questionnaire has been posted. The questionnaires will be linked to the participant by attaching the study code (documented in the log book) to the inside of the front cover of each booklet.

### Analysis

The analysis will be by ‘intention to treat’, including withdrawals and losses to follow-up. Randomisation should ensure that the groups are similar or equivalent in their baseline characteristics; additional multivariate analysis will be used if baseline differences are noted between the two groups. The relative risks (with 95% confidence intervals) of the primary outcomes will be calculated. Secondary outcome measures of categorical data will be analysed with χ^2^ tests and continuous data will be analysed with t-tests (for normally distributed data). Ranked or Likert-scale data will be analysed using cumulative odds ratios. Logistic regression and multiple linear regressions will be used if necessary to adjust for any other confounding variables.

It is not possible to blind participants to the model of care they receive, but outcome assessments will be blinded.

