## Methods/Design

The study uses a two arm, un-blinded randomised controlled design, to compare the outcomes for women who had midwifery continuity of care compared with those who had standard maternity care.

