### Trial recruitment

Women telephone the booking office to book for maternity care and receive an appointment for their first/booking-in visit. The women will be initially screened by the booking clerk for eligibility into the trial according to the eligibility criteria. An information pack about the study is posted to all eligible women. At the first/booking-in visit, the research assistant (RA) approaches each eligible woman and asks if she received the information and whether she is interested in participating. If the woman agrees, the consent form is signed and the woman is registered as a trial participant and the remote telephone allocation service at the university is contacted for random allocation.

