### Group allocation

Randomisation will be on a 1:1 basis. Allocation concealment will be assured by using a remote telephone allocation service through the university research department. The RA will telephone the university to provide the woman’s initials, medical record number and date of birth. The clerk at the university campus will allocate women based on a randomization schedule developed independently from the RA. The midwife will be informed of the group to which the woman has been allocated and will receive her study number, which will be recorded in the Trial Register and Log Book. If allocated to standard care, the woman will be advised of her next clinic appointment. If allocated to midwifery continuity of care, she will be advised that the continuity of care midwives will contact her with a suitable appointment time.

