### Data collection

#### Clinical data

The majority of clinical data required for the study are routinely collected and available in hospital records. The RA will collect these data and 5% of the records will be double checked by one of the CIs to verify their accuracy and consistency.

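### The claim that outcome assessments are blinded cannot hold for the self-reported questionnaires, and no step described supports it for the clinical outcomes, including attempted VBAC

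*Protocol article*

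**What the plan says.** The blinding statement closes the main part of the Analysis section: "It is not possible to blind participants to the model of care they receive, but outcome assessments will be blinded". Methods/Design describes the trial differently: "The study uses a two arm, un-blinded randomised controlled design".

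The tasks around allocation and data collection are assigned as follows.

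- Trial recruitment: at the booking-in visit "the research assistant (RA) approaches each eligible woman and asks if she received the information".
- Group allocation: "The RA will telephone the university to provide the woman’s initials, medical record number and date of birth". A university clerk allocates, and then "The midwife will be informed of the group to which the woman has been allocated and will receive her study number".
- Clinical data: most items come from routine hospital records. "The RA will collect these data and 5% of the records will be double checked by one of the CIs"; the stated purpose of that check is accuracy and consistency.
- Women's experiences: two questionnaires, at 36 weeks and at 6-8 weeks after birth, cover experience of care, planned mode of birth, DASS 21, the Edinburgh scale and decisional conflict; the postnatal one adds satisfaction with decisions. "These will enable women to report on their experiences with the model of care".
- Administration of questionnaires: the RA contacts women to say that the questionnaire has been posted.
- Data safety and monitoring: the committee that reviews safety and serious adverse events is blinded to group.

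**The concern.** Blinded outcome assessment is one of the features by which readers and systematic reviewers judge an open-label trial. Here it is claimed for all outcomes at once, while the procedures described show it for safety review only.

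Two groups of outcomes are affected. The questionnaire outcomes serve the stated secondary aims on emotional outcomes and experience of care, and they are open to influence from knowing which service one received. The primary outcome, attempted VBAC, is less objective than mode of birth or death. Someone must decide from the record whether an attempt took place, for example when a woman booked for repeat CS goes into labour first. If the person deciding knows the arm, doubtful cases may be settled differently in the two groups. The trial would then be credited with a protection that its described procedures do not provide.

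**Working it through.** This is mainly a comparison of sections; arithmetic enters only as an illustration.

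**Step 1. Questionnaire outcomes.** Under Women's experiences, the woman completes the instruments, so she is the assessor. Under Analysis, she cannot be blinded. The second half of the Analysis sentence is therefore false for these outcomes by its own first half. No further operational detail could reconcile the two.

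**Step 2. Clinical outcomes.**

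| Task | Section | Who | Blinding stated? |
|---|---|---|---|
| Approach at booking-in | Trial recruitment | RA | Not applicable (before allocation) |
| Allocation call | Group allocation | RA calls, clerk allocates | No; the midwife is told the group, the RA is not mentioned |
| Extraction from hospital records | Clinical data | RA | No |
| 5% double check | Clinical data | An investigator (CI) | No; for accuracy and consistency |
| Questionnaire contact | Administration of questionnaires | RA | No |
| Safety and serious adverse event review | Data safety and monitoring | Committee | Yes |

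One role makes the allocation call and later extracts the outcomes. The arms also differ in who gives the care: a small group of midwives, or different staff at each stage. Records of that care may therefore point to the arm, although the document does not say so. No separate assessor and no masking of records is described.

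**Step 3. The plan's own figures, for context.** Sample size sets 35% against 52.5% with 80% power and α = 0.05. A two-sided comparison of two proportions with continuity correction gives 137 per arm, so 2 × 137 = 274, as stated. Allowing for 15% loss gives 274 / 0.85 = 322.4, hence 323; the plan states 332, or 166 per group. Nothing in the blinding point depends on that gap. The target difference is 52.5 − 35 = 17.5 points.

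**Step 4. Illustration of size.** The document gives no rate of doubtful cases. Assume that a net share m of women in one arm is misclassified in the same direction and none in the other arm. The difference in proportions then shifts by m.

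- m = 1%: 0.01 × 166 = 1.7 women; shift 1 point; 1 / 17.5 = 6% of the target.
- m = 2%: 0.02 × 166 = 3.3 women; shift 2 points; 2 / 17.5 = 11%.
- m = 4%: 0.04 × 166 = 6.6 women; shift 4 points; 4 / 17.5 = 23%.

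One-sided misclassification is the unfavourable case. Errors in the same direction in both arms would partly cancel.

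**The case against.** The strongest reply is that this is a condensed article of a trial openly called un-blinded. In such a trial, blinded outcome assessment usually refers to those who extract or classify clinical data, and who does this from which material is detail for the full protocol. That has force for the clinical outcomes, and it is why the point there is that the claim is unsupported rather than disproved. It does not rescue the questionnaire outcomes, for which the sentence makes no exception.

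Several stronger readings are tempting, and the documents do not support them.

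- *The RA is unblinded.* Group allocation names only the midwife as informed. The RA is a role across two sites, and nothing says that one person does every task for one woman. Since allocation follows the RA's call, knowledge of the arm is a strong inference, but it is not stated.
- *Nothing is assessed blind.* The safety committee is. Questionnaires also carry a study code, which is compatible with masked scoring, although masking is not stated.
- *The primary outcome is planned mode of birth.* Sample size names attempted VBAC. The plan before labour or CS is a separate item in the pregnancy data. The hypothesis speaks of choosing to attempt, but that looseness of definition is a separate matter from blinding.
- *The primary result will be biased by a known amount.* Nothing in the document indicates how often an attempt is ambiguous.

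Mode of birth and deaths are fairly objective, so any effect on them is probably small.

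**Conclusion.** The statement is wrong as written for the questionnaire outcomes and unsupported for the clinical outcomes, the primary included. It is supported for safety and serious adverse event review only.

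The first conclusion needs no assumption beyond the text. The second rests on one role making the allocation call and extracting the data, with no masking described; it would fall away if an assessor without knowledge of the allocation exists and were named. The size of any bias is unknown. The 6-23% of the target effect is what an assumed 1-4% of one-directional misclassification in one arm would produce, not an estimate. The trial is not invalidated, but the claim should be corrected, because it overstates the protection against ascertainment bias.

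**What to change.** 1. Limit the Analysis sentence to what is assessed blind, namely safety and serious adverse event review by the committee. State that participants, carers and the self-reported questionnaire outcomes are unblinded.
2. For attempted VBAC, do one of two things. Either name an assessor who does not know the allocation, or have an investigator already assigned to the double check classify this one field in all 332 women. The existing 5% check is not described as masked, so those records need it too. The classification should follow one fixed written rule for what counts as an attempt. It should use an extract that gives the relevant record entries rather than the RA's own coding, and that omits allocation and carer names.
3. Keep attempt as the endpoint. Scoring it from the planned mode of birth would change what is measured, since a woman planning VBAC may have a CS before labour.

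The cost is the preparation of the extracts, one field to classify in 332 records, and a less favourable description of blinding. No new staff, visits or change in sample size are needed. If a blinded assessor already exists, naming the role and the outcomes covered settles the clinical part; the statement on the questionnaires must still be corrected.

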#### Interim analysis

A multidisciplinary data-monitoring group has appointed at the outset of the study to monitor the safety of the trial particularly examining differences between the groups that may be larger than expected and assessing any serious adverse effects that may occur. After 50% of the women have enrolled, a difference of at least three standard deviations in the interim analysis of a major endpoint will be needed to justify stopping the trial.

### Confidentiality and data security

All paperwork, documentation, internet and audiotaped data will be treated with confidentiality. The log books required on–site are kept in the office of the booking clerk. This office is staffed during business hours, and is only used by one staff member. The door is locked when the room is empty. Hard copies of client details and study matters are kept in a filing cabinet within the locked area at the university.

### Ethical aspects

Human Research Ethics Committee (HREC) approval for all current sites has been provided by the North Sydney Central Coast HREC, according to the single site HREC approval for multicentre clinical trials guidelines. Research governance approval has been provided by the Research Governance Office at each site.

### Data safety and monitoring

A Data and Adverse Event Monitoring Committee will assess the safety and serious adverse events and will be blinded to the assigned group. Serious adverse events will be given a Severity Assessment Code consistent with incident monitoring in NSW [35] and reviewed by the Committee. Any perinatal deaths will be analysed to determine whether the model of care contributed.

### Interruption of the study

The CIs may terminate this study prematurely, either in its entirety or either of the sites, for reasonable causes (e.g. unsatisfactory enrolment with respect to quantity or quality, inaccurate or incomplete data collection, falsification of records, failure to adhere to protocol). If this occurs, the site investigator will provide written notice to the CIs of the intended termination.

## Discussion

One of the greatest contributors to the overall CS rate is women having elective repeat CS. In this study, we will test the effects of midwifery continuity of care (where women have the same midwives through pregnancy and during labour and birth) on rates of vaginal birth and other outcomes in women with a prior CS. This will be the first Australian and international randomised controlled trial of midwifery continuity of care that focuses on women who have had a previous CS. High level evidence on midwifery continuity of care shows that these models increase women’s sense of control over decision making [22] hence the link in our hypothesis – that is, increased control will impact on decision making and increase rates of attempted vaginal birth.

Pregnancy, birthing and early parenthood are profoundly important life experiences that directly affect almost 300,000 families in Australia each year. An increasing CS rate is of national and international concern. The Editor of the prestigious journal Birth wrote in 2007 “reducing the caesarean birth rate worldwide is a complex and difficult task that must be tackled on many fronts using multiple strategies” [36]. A key finding of the Maternity Services Review in Australia was that the CS rate was higher than many similar countries and this highlighted the need for more research in this area [2]. The Australian National Maternity Services Plan [37] has also drawn attention to the fact that the high rates of caesarean section are often compounded by a lack of support for vaginal births after caesarean section providing preliminary evidence that midwifery continuity of care will indeed increase VBAC.

This will be the first national and international trial that has tested midwifery continuity of care as an intervention to increase vaginal birth rates in women who have had a previous CS. Although a number of studies have focused on interventions that improve the rates of attempted and/or successful VBAC, they have not been able to demonstrate their effectiveness. This study will provide this evidence that can be used to improve maternal outcomes while maintaining the safety of Australian mothers and babies.

